### Follow up visits

Participants will be included in the FENICE study for a total of 24 months and will be followed up differently based on the inclusion arm. In the study arm (APA and Mediterranean diet arm) patients will be monthly followed up for comorbidities, co-medication and herbal remedies, adverse events, and body mass index (BMI). Moreover, every three months also clinical evaluation, blood parameters, instrumental exams and QoL questionnaires will be carried out for the study arm patients. In the control arm, instead, all the mentioned parameters will be followed up every three months (see **Figure 2**).

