### Data collection

Participants will be included in the study and will undergo several follow-up visits. During the follow-up period trained research nurses/data managers will contact patients at baseline (T=0) (± one week), and subsequently every four weeks (± two weeks), to go through a standardized questionnaire and to collect data on the outcomes of sequelae and clinical symptoms/AEs. In addition, all patients will be contacted by the research nurse/data manager at the end of the APA period (± two weeks from the end) to complete a last questionnaire. Research nurses/data managers additionally will collect required laboratory and or test results from participants’ (electronic) medical records. If a subject discontinues the APA and lifestyle interventions during the 12-week follow-up period, follow-up will continue.

The questions within the surveys will be performed to assess the occurrence and severity of any new symptoms experienced by the participants, and the global physical and psychological health after the beginning of APA. The questionnaires that will be administered to participants during the study period are listed in **Table 4**.

**Table 4 T4:** Type of questionnaire that will be administered to breast cancer patients.

Objective	Questionnaire
**Disability**	The DASH (disabilities of the arm, shoulder, and hand measurement tool) questionnaire
**QoL**	EORTC qlq-C30 and EORTC qlq- BR23 questionnaire
**Fatigue**	The MFI 20 (Multidimensional fatigue inventory) questionnaire
**Anxiety-depression**	The HADS (Hospital anxiety and depression scale) questionnaire
**Physical activity and sedentary behavior**	The short version of the IPAQ (international physical activity questionnaire)
**Oedema assessment**	Disability scale for oedema

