### Sample size

The hypothesis guiding the formal determination of the sample size proposes an expected improvement of at least 15 points in the mean DASH score. The DASH score is a valuable, pragmatic, and frequently utilized metric in individuals with various musculoskeletal disorders of the upper limb. Ranging from 0 to 100, it encompasses responses to 30 questions (https://orthotoolkit.com/dash/) An improvement of at least 15 points is considered clinically significant in enhancing functional ability. The statistical parameters are configured in a highly conservative manner, considering the non-pharmacological nature of the intervention (adapted physical activity) and the inherent inter-individual variability in response, particularly within the treated group (Group 1). Therefore, with alpha and beta errors set at 0.01, a standard deviation in Group 1 that is twice that of Group 2 (SD: 20 compared to 10), even exceeding the hypothesized difference (15 points), 56 patients per group are deemed necessary. Considering the enrollment capabilities of our group and potential physiological withdrawal of patients, the sample size has been increased to 150 total patients. The target population will be at least 18 years of age (of any ethnicity) with a diagnosis of non-metastatic breast cancer and already treated with surgery for the primary tumor. This total will be divided into two sub-groups by randomization in blocks of 75 patients each (intervention group, Group 1, and control group, Group 2). The first group will be distinguished by subjects treated with adapted physical activity rehabilitation and with correct lifestyle suggestions. The second group, on the other hand, will be characterized by standard care without physical activity rehabilitation or lifestyle suggestions.

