### Statistical analysis

The descriptive statistical analyses, the central tendency, variability, symmetry and kurtosis will be calculated, all accompanied by appropriate graphical representations. Regarding the inferential analyses, we will continue with the verification of the parametric and non-parametric hypotheses, respectively for the quantitative variables with parametric tests such as: Student’s t-test, Fisher’s F-test, etc. and for categorical variables using non-parametric tests such as: chi-square, Mann Wittney’s U, Fisher’s exact test, etc. Only results with p-values ≤ 0.05 will be considered statistically significant. Principal component analysis (PCA) will be adopted to explore the relationships among secondary variables and identify patterns of improvement related to the APA intervention (50).

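### The tests named for quantitative outcomes use one value per woman in a design with three-monthly visits, so selective loss that differs between arms can bias the DASH comparison; a repeated-measures model would be better

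*Protocol article*

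**What the plan says.** All references are to the protocol article.

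- **Statistical analysis.** Methods for quantitative outcomes are introduced "respectively for the quantitative variables with parametric tests such as" Student's t-test and Fisher's F-test, and the list is left open. No test is assigned to DASH or to a visit. No method that uses repeated measurements is named; principal component analysis is reserved for exploring secondary variables.
- **Follow up visits.** In the study arm, "every three months also clinical evaluation, blood parameters, instrumental exams and QoL questionnaires will be carried out for the study arm patients". For controls, "In the control arm, instead, all the mentioned parameters will be followed up every three months".
- **Data collection.** Contacts occur at baseline and "subsequently every four weeks (± two weeks), to go through a standardized questionnaire". Table 4 lists "The DASH (disabilities of the arm, shoulder, and hand measurement tool) questionnaire" under disability, separately from the quality-of-life instruments, and gives no time points for it. On stopping the intervention: "If a subject discontinues the APA and lifestyle interventions during the 12-week follow-up period, follow-up will continue".
- **Sample size.** DASH drives the sizing: a 15-point difference, SD 20 and 10, alpha and beta 0.01, 56 women per group. Then: "Considering the enrollment capabilities of our group and potential physiological withdrawal of patients, the sample size has been increased to 150 total patients".
- **Design of FENICE trial.** A minimum of 48 sessions over six months is set for assessing the primary endpoint. Only the study arm has sessions.
- **Ethical considerations.** Women with complications that endanger their health will be asked to withdraw from the study.

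**The concern.** The design collects a series of measurements, but each named test, as ordinarily applied, compares the arms on a single value per woman. If that value is the endpoint DASH or its change from baseline, a woman who leaves before the endpoint visit adds nothing, even if she was measured earlier.

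That is harmless when loss is unrelated to arm function. It is not harmless when women doing worse are more likely to be lost and this acts differently in the two arms. Three features of the article make such a pattern plausible:

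- Withdrawal from the study is tied to health complications.
- The session minimum for assessing the primary endpoint has no counterpart in the control arm.
- The study arm is reviewed monthly for adverse events and the control arm every three months, so complications can surface sooner in the study arm.

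At stake is a shift toward fencing among completers with no true effect, and a false-positive rate above the nominal 5%. This is separate from adjusting for baseline or allowing unequal variances, since either can be done on completers alone.

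**Working it through.** **1. The plan's sample size.** Inputs from Sample size: difference 15, SD 20 and 10, alpha 0.01, beta 0.01.

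Normal approximation, two-sided: n = (20² + 10²)(2.576 + 2.326)² / 15² = 500 × 24.03 / 225 = 53.4, so 54 per group. With the noncentral t distribution it is exactly 56 per group, so the stated figure reproduces.

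**2. Headroom for loss.** (150 − 112)/150 = 38/150 = 25.3%. This is a ceiling, because the article also credits the increase to enrolment capability.

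**3. Power is not the issue.** With 56 per group, power for 15 points is about 0.990 at two-sided 0.01 and 0.999 at two-sided 0.05. The concern is bias.

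**4. Size of the bias by direct arithmetic.** Let d be the share missing in an arm and D the number of DASH points by which the missing women are worse than completers. The bias in the completers' difference is d₁D₁ − d₀D₀. Assume d₁ = 0.25 in the fencing arm and unselective loss in controls (D₀ = 0). The standard error with 56 per group is √(500/56) = 2.99.

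| D₁ (points, assumed) | Bias toward fencing | True-null rejection at 5% |
|---|---|---|
| 5 | 0.25 × 5 = 1.25 | 7% |
| 10 | 2.5 | 13% |
| 15 | 3.75 | 24% |
| 20 | 5.0 | 39% |

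If both arms lose 25% and D is the same number of points in each, the bias is 0.

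**5. Simulation.** Assumptions: 75 per arm; DASH at baseline, month 3 and month 6; SD 20 and 10; between-visit correlation 0.6; no true difference; about 25-30% missing at month 6; logistic dropout after month 3. Completers are compared by a Welch t-test. The comparator is a likelihood analysis that also uses baseline and month 3.

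| Loss pattern | Completers' bias toward fencing | Rejection, completers |
|---|---|---|
| Random | 0 | about 5% |
| Log-odds 0.9 per SD of month-3 DASH, both arms | about 1.3 points | about 7% |
| Log-odds 0.6 to 1.2 per SD, fencing arm only | about 1.7 to 3.4 points | about 9% to 20% |

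In the fencing-only pattern the likelihood analysis has bias of about 0 and rejects in 4-5% of trials. Under random loss its standard error is 2.83 against 3.00, which is (3.00 − 2.83)/3.00 = about 6% smaller.

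The middle row is not zero because of the plan's own unequal SDs. The same slope per SD produces twice as many points of selection at SD 20 as at SD 10, so the arms cancel only in part: about 2.5 − 2.5 × 10/20 = 1.25.

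With 10% loss instead, in the fencing-only pattern, bias falls to about 0.6-1.3 points and rejection to 6-8%.

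**The case against.** Much of the opposing case stands.

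- **No completers-only rule is written.** A reader might infer that the plan discards women without the endpoint visit. The article does not say so. The test list is open, and an F-test could be a variance ratio or an analysis of variance. Missing-data rules and analysis populations are commonly left to the full protocol or analysis plan, so their absence is no finding.
- **No dropout rate is stated.** A reader might take 25% as expected withdrawal. It is only the most the sizing could absorb.
- **Three-monthly DASH is inferred.** The schedule refers to quality-of-life questionnaires, while Table 4 puts DASH under disability. A reader might conclude that month-3 DASH values are collected and thrown away; the article does not establish that they are collected.
- **Follow-up continues after stopping the intervention.** Leaving fencing is therefore not the same as losing the DASH value. This protects only in part: the sentence refers to a 12-week period, whereas the primary endpoint needs at least six months of sessions. It also does not reach women withdrawn from the study itself.
- **The simulation favours the remedy.** Dropout depends on the month-3 value that the likelihood analysis conditions on, so its near-zero bias is built in. That is why a sensitivity analysis belongs with the model.

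What remains is a mismatch in what the article does state: the only named methods for quantitative outcomes are generic tests that make no use of the repeated visits.

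**Conclusion.** The point holds as a weakness in the named method, not as a demonstrated bias. The article schedules repeated assessments and leaves room for up to 25.3% loss, then names tests that in ordinary form use one value per woman. Bias arises only if loss is selective and its effect differs between arms. The article's withdrawal and session provisions make that plausible; they do not show that it will occur.

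Under the stated assumptions the bias runs from 0 to about 3.4 DASH points, against a 15-point target, with true-null rejection between about 5% and 20% at nominal 5%. The dropout strength, the correlation of 0.6, the amount missing and the month-3 DASH are all assumptions. The documents do not support a stronger statement that the DASH result is biased, and the loss of power is negligible. The change is still worth making before outcome data are seen, because the better method costs little.

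**What to change.** In Statistical analysis, name a mixed model for repeated measures as the analysis of DASH and the other three-monthly quantitative outcomes:

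- Include all randomised women and all collected visits.
- Fit terms for arm, visit, arm-by-visit and baseline, with arm-specific variances, since the sizing itself assumes SD 20 and 10.
- Test the arm difference at the visit designated as primary.

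In Follow up visits or Table 4, state that DASH is among the three-monthly questionnaires in both arms. Add one delta-adjusted sensitivity analysis in which missing fencing-arm DASH values are made progressively worse.

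The cost is a few lines of wording and a little programming. No new data are needed if DASH is already part of the three-monthly set; if it is not, one questionnaire is added at those visits. The downside is that the model assumes data are missing at random given the observed visits, which the sensitivity analysis probes.

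### The sample size assumes a 4:1 variance ratio between arms, but the only two-sample test of means named is Student's t-test, which is miscalibrated under those SDs if the arms end unequal in size

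*Protocol article*

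**What the plan says.** Protocol article, Sample size: the hypothesis "proposes an expected improvement of at least 15 points in the mean DASH score". The calculation is run "with alpha and beta errors set at 0.01" and uses "a standard deviation in Group 1 that is twice that of Group 2 (SD: 20 compared to 10". The wider spread is put down to variable response among treated women. The result is that "56 patients per group are deemed necessary". To allow for enrolment capacity and "potential physiological withdrawal of patients, the sample size has been increased to 150 total patients", the total is raised, and "This total will be divided into two sub-groups by randomization in blocks of 75 patients each".

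Protocol article, Statistical analysis: quantitative variables are to be tested "for the quantitative variables with parametric tests such as: Student’s t-test, Fisher’s F-test, etc". Mann-Whitney is listed with the tests for categorical variables. Significance is declared at p ≤ 0.05. No test is assigned to DASH by name.

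Protocol article, Data collection: staff will "contact patients at baseline (T=0) (± one week), and subsequently every four weeks", and Table 4 lists DASH among the questionnaires. I take it from this that a baseline DASH score will exist.

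**The concern.** Two neighbouring sections rest on different assumptions. The sizing takes the intervention variance as four times the control variance (400 against 100). The analysis section names a test that pools the two variances into one. The other named procedure does not help. If Fisher's F-test means analysis of variance, then with two arms it is the square of Student's t and carries the same assumption. If it means a variance-ratio check, it does not compare means.

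Pooling is harmless when the arms are equal in size. When they are not, the pooled variance gives most weight to the larger arm. If the more variable arm is the smaller one, the standard error is too small, so p-values are too low and confidence intervals too narrow. If it is the larger one, the test is conservative. The calibration of the main DASH comparison would then depend on which arm loses more women.

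**Working it through.** **Inputs.** From Sample size: difference 15 points, SD 20 (intervention) and 10 (control), alpha 0.01, beta 0.01, 56 required and 75 planned per arm. From Statistical analysis: threshold 0.05. Sidedness is not stated, so two-sided is an assumption.

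**1. The plan's own figure.** Normal approximation:

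n = (SD1² + SD2²)(z₀.₉₉₅ + z₀.₉₉)² / δ² = (400 + 100)(2.576 + 2.326)² / 15² = 500 × 24.03 / 225 = 53.4, so 54 per group.

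With the noncentral t distribution the smallest n reaching 99% power is 56, both with Welch degrees of freedom (power 0.9904) and with pooled degrees of freedom (0.9911). One-sided it would be 50. The stated 56 is therefore reproduced exactly, two-sided, with unequal SDs. Welch's test needs no extra patients.

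**2. Standard errors.**

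- True: √(SD1²/n1 + SD2²/n2).
- What Student's test estimates: √(s_p²(1/n1 + 1/n2)), with s_p² = [(n1 − 1)SD1² + (n2 − 1)SD2²] / (n1 + n2 − 2).

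At 56 intervention and 75 control:

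- s_p² = (55 × 400 + 74 × 100) / 129 = 227.9
- pooled SE = √(227.9 × (1/56 + 1/75)) = 2.67
- true SE = √(400/56 + 100/75) = 2.91
- ratio 2.67 / 2.91 = 0.92, so intervals are about 8% too narrow.

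At 75/75, s_p² = 250 and both standard errors equal √(500/75) = 2.58, so there is no distortion.

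**3. Type I error at two-sided nominal 0.05.** Simulated with normal data, no difference in means, SD 20 and 10, and 400,000 replicates per row:

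| Intervention / control | Pooled SE | True SE | Student | Welch |
|---|---|---|---|---|
| 75 / 75 | 2.58 | 2.58 | 0.050 | 0.049 |
| 65 / 75 | 2.62 | 2.74 | 0.061 | 0.050 |
| 60 / 75 | 2.64 | 2.83 | 0.068 | 0.050 |
| 56 / 75 | 2.67 | 2.91 | 0.074 | 0.050 |
| 75 / 56 | 2.91 | 2.67 | 0.033 | 0.050 |

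At nominal 0.01, the level used for sizing, Student's test gives about 0.010 at 75/75, 0.019 at 56/75 and 0.005 at 75/56.

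The 56/75 row means that the intervention arm uses its whole margin (19 of 75, or 25.3%) and the control arm loses nobody.

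**4. Baseline adjustment.** Relative to an unadjusted comparison of final scores, ANCOVA multiplies the variance by about 1 − r², where r is the correlation between baseline and follow-up DASH. The article gives no r. For assumed values, taking one r for both arms:

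- r = 0.3: 1 − 0.09 = 0.91
- r = 0.5: 1 − 0.25 = 0.75
- r = 0.7: 1 − 0.49 = 0.51

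That is a reduction of 9% to 49%. Power for 15 points at 75 per arm is already about 99.9% at alpha 0.01, so the stated power does not depend on this gain.

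**The case against.** **The list is open.** It is worded as examples, covers all quantitative variables and is not tied to DASH, so Student's test is not fixed as the primary analysis and Welch is not excluded. This stands. The point is only that the one comparison of means actually named does not match the sizing.

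**The arms are planned equal.** This stands too. At 75/75 there is nothing to correct.

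**The loss scenarios are one-sided.** If both arms lose women the effect is smaller: about 0.062 at 56/66 and 0.057 at 64/70. A reader might infer that heavier loss from the fencing arm is the expected pattern, since the sessions, the diet and the monthly visits fall on that arm. The article does not support that. Sample size mentions withdrawal without a rate or an arm. Adaptation of fencing activity expects few women to drop out. Data collection continues follow-up after the intervention is stopped. Heavier control loss is possible, and the test would then be conservative.

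**SD 20 against 10 is a cautious sizing input.** If the extra spread is variation in response, an intervention without any effect would produce no extra spread, and Student's test would be valid. The simulated null needs an intervention that widens the spread without moving the mean. With SD 15 against 10 the error at 56/75 is about 0.064 to 0.065. This limits the size of the problem. It does not justify pooling variances that the protocol itself expects to differ, and an interval for a real effect would still be affected.

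**Silence on baseline DASH.** A reader might infer that the plan wrongly ignores the baseline score. The article does not show this. The improvement in DASH may already mean change from baseline, and covariate adjustment is commonly left to an analysis plan that is not shown.

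**Conclusion.** The mismatch is real and its effect is conditional and modest. Under the protocol's own SDs, Student's t-test keeps its level at the planned equal arms. At nominal 0.05 it drifts to about 0.061 to 0.074 if the intervention arm ends with 65 down to 56 women against 75 controls, and to about 0.033 at 75/56. Welch's test stays at about 0.05 throughout and keeps the required number at 56 per group.

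This rests on the stated SDs, normal data, a two-sided test and assumed patterns of loss. It does not support saying that the trial's error rate is uncontrolled or that inflation is the expected outcome. Nor is the absence of baseline adjustment an error. It is worth correcting because the better method costs nothing.

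**What to change.** In the Statistical analysis section, replace Student's t-test for DASH with one named analysis that allows the variance to differ by arm, as the sizing does. Either of these would do:

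- Welch's t-test; or
- preferably, ANCOVA of DASH on arm and baseline DASH, with heteroscedasticity-robust standard errors or an arm-specific residual variance.

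The second also gains whatever precision the baseline score offers. The choice should be written down before any outcome is examined by arm. The cost is wording only: no further patients, and no data beyond the baseline and follow-up questionnaires already planned.

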## Discussion

Regular physical activity performed during and after a BC treatment has been shown to improve quality of life (QoL) (34, 35). However, the type of exercise and the time spent on it are still based on patient’s will. Recently, a rehabilitation program was launched in France for women treated for BC that used adapted fencing as a rehabilitative activity. The RIPOSTE program aimed to offer adapted fencing to patients with BC (30, 43). In Italy, several authorities, including scientific associations (LILT – Lega Italiana per la Lotta ai Tumori), sports federations and Institutions (FIS – Federazione Italiana Scherma, CONI – Comitato Olimpico Nazionale Italiano) are committed to raising awareness of cancer patients and physicians on APA, diet, and correct lifestyle, throughout the promotion of observational studies, sporting, and popular events (“Nastro rosa”, “rema Roma per la vita”). With the FENICE study protocol, the initiative is intended to introduce the discipline of fencing into the rehabilitation program for women who have undergone surgery for breast cancer. Usually, after surgery, there is excessive internal rotation of the shoulder, which affects the patient’s posture, and fencing, especially the guard position, promotes an improvement of this condition. In addition, the range of motion resulting from increasingly higher parries under the guidance of the fencing master promotes the mobility of the arm and shoulder, which are limited by surgical scars and adhesions. The laterality of the exercise and the type of weapons used (foil and saber) allow constant work on mobilizing the operated shoulder and arm, especially since it is an upper-body activity that focuses on the upper body, from the belt to the head. (30, 43). Finally, the strong concentration and determination that fencing requires will certainly have a positive effect on image, mood, and mental strength, which are very often compromised following breast surgery. We firmly believe that the FENICE study by introducing adapted fencing in the near postoperative period, can be an effective tool to improve the physical and mental health of patients who have undergone surgery for BC. To date, the importance of adapted physical activity as a rehabilitation measure is emphasized in the literature, especially for cancer patients. In Italy, however, APA remains limited to local initiatives without being promoted by the health authorities. In some countries, such as France and the United Kingdom, APA is recognized as a prescription treatment for chronic diseases. As APA is therefore reimbursed by the health system, the sports doctor can prescribe a physical rehabilitation activity such as a medication or an examination. We hope that the FENICE protocol will be a pilot study for large-scale clinical trials that can lay the foundations for nationwide recognition of APA in the Italian healthcare system. Alongside the key role of the sports physician in APA implementation, this initiative might shed light on the role of physical activity and rehabilitation in improving WA of breast cancer patients since data from the literature are to date inconsistent (51). Currently, there is a lack of uniform and shared guidelines that can evaluate the Work Ability Index (WAI) through interventions or rehabilitative activities that support the patient’s return to work or, possibly, retention. Recently, the “Beyond Cancer” program by Sheppard and colleagues tried to overcome these barriers to sustainable return to work for women with breast cancer (52). In that perspective the FENICE study, as a tailored occupational rehabilitation intervention, may also include in its multidisciplinary network occupational physicians to assess the actual benefit of PA in promoting patients’ return to work and employability through dedicated questionnaires for participants in the adapted fencing group.

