### Secondary objective

The secondary aim is to compare whether APA improves perception of cancer-related fatigue (CRF) and sleep quality (both measured via specific questionnaires), BMI, bone health, aerobic capacity, heart rate and serum lipid profile in the study arm. In addition, levels of Work Ability as well as health care provider and patient attitudes toward APA as adjunctive therapy will be assessed. Finally, the effect of adapted physical activity and a healthy diet on reducing the recurrence of the disease is being investigated.

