Adapted fencing includes offensive and defensive actions, which are performed considering the mobility of the shoulder. The primary (tierce = outside; quart = inside; fifth = head) and secondary blocks are therefore performed by patients with maximum mobility, without ever causing pain. Coordination, agility, and strength are encouraged during exercises between patients and during lessons with the fencing master. The adapted fencing lesson ends with a cool-down period. Since different subjects experience different physical outcomes for the cancer and the subsequent treatment, the program must address these individual needs while respecting safety principles. Therefore, rest and water breaks will be provided when necessary, and simplified or less strenuous movements will be suggested as alternatives for those who find parts of the workout too challenging or unsafe. In addition, participants are encouraged to use both saber and foil, also depending on which master is holding the training session. In any case, the weapons used will be adapted in material to avoid excessive strain or fatigue as stated above. Moreover, the courses and masters allow 12 participants per session with a maximum ratio of 1 master per 2.5 participants. During the study protocol, participants are also encouraged to follow healthy diet and adhere to the standards of the Mediterranean diet through the prescription of a personalized diet by a nutritional biologist involved in the project. Conventional bioelectrical impedance (BIA) testing to assess body composition is also planned during protocol follow-ups. To assess adherence to the Mediterranean diet, the Prevención con Dieta Mediterránea (PREDIMED) questionnaire will be completed both at the beginning and at the end of the study (49). The participants of the FENICE study will be followed up by several specialists before and during the APA period (**Figure 3**). This study was approved by the ethic board of the Policlinico Tor Vergata of Univeristy of Rome and the enrollment will start in September 2024 and the recruitment will take an 18 months’ time window for the inclusion of the expected 150 participants.

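### Work Ability is listed under the secondary objective, but the only work-outcome collection described is optional and confined to the fencing arm, so as described no between-arm comparison is possible

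*Protocol article*

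**What the plan says.** - **Secondary objective:** after a list of outcomes to be compared, a separate sentence adds "In addition, levels of Work Ability as well as health care provider and patient attitudes toward APA as adjunctive therapy will be assessed". It names no instrument and no arm.
- **Discussion:** the study "may also include in its multidisciplinary network occupational physicians to assess the actual benefit of PA" in promoting "return to work and employability through dedicated questionnaires for participants in the adapted fencing group". Just before this, the Discussion mentions the Work Ability Index, calls the literature on activity and work ability inconsistent, and hopes the trial will shed light on it.
- **Data collection:** "The questionnaires that will be administered to participants during the study period are listed in" Table 4. The table covers arm disability (DASH), quality of life (EORTC QLQ-C30 and BR23), fatigue (MFI-20), anxiety and depression (HADS), physical activity (short IPAQ) and oedema. It has no work-ability row.
- **Follow up visits:** "In the control arm, instead, all the mentioned parameters will be followed up every three months". The parameters mentioned are comorbidities, co-medication and herbal remedies, adverse events, BMI, clinical evaluation, blood parameters, instrumental exams and quality-of-life questionnaires.
- **Sample size:** 150 women, 75 per arm.

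**The concern.** The Discussion states a causal aim, the benefit of activity for work, and then describes data from one arm only. Women enter within four weeks of surgery and, according to the Figure 2 legend, are followed for 12 to 24 months. Work status can be expected to change over that time with or without fencing. A before-after change in the fencing arm would count all of that recovery as benefit, and the protection of randomization would be lost for this outcome.

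This goes beyond a detail left to an analysis plan. The article says who would receive the questionnaires, and no analysis can recover control-arm data that were never collected. Because the Discussion presents the evidence on work ability as unsettled, an uncontrolled estimate would do little to settle it.

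**Working it through.** The article gives no figure for work outcomes, so there is none to reproduce. Its one calculation (15 DASH points, SDs 20 and 10, alpha and beta 0.01) does reproduce: a two-sided t-test needs 56 per group. This point does not depend on it.

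**Step 1. Trace the work outcome through the article.**

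| Section | Work measure in fencing arm | Work measure in control arm |
|---|---|---|
| Secondary objective | to be assessed, arm not stated | to be assessed, arm not stated |
| Data collection, Table 4 | none listed | none listed |
| Follow up visits | none listed | none listed |
| Discussion | questionnaires, optional | none |

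If the Discussion's add-on goes ahead, work data come from up to 75 women in one arm and 0 in the other. If it is dropped, no collection is described in either arm. Neither case allows a comparison.

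**Step 2. What a one-arm estimate measures.** Let τ be the effect of the intervention and C the mean change under usual care over the same period.

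- Expected change in the fencing arm: τ + C.
- Expected difference in change between arms: (τ + C) − C = τ.

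Used alone as an estimate of τ, the fencing-arm change has bias C. If τ = 0, it still shows C. The documents give no value for C, so the size of the bias is left as C. It is zero only if usual care brings no change in work outcomes.

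**Step 3. Could the trial support the comparison?** Let σ be the SD of a work-ability score, assumed equal in both arms. The standard error of the difference in means is σ × √(2/n).

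- n = 75 per arm: σ × √(2/75) = 0.163σ; 95% half-width 1.96 × 0.163σ = 0.32σ.
- n = 56 per arm (the calculated size before the increase): σ × √(2/56) = 0.189σ; 95% half-width 1.96 × 0.189σ = 0.37σ.

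Fewer women may contribute, since Table 3 admits women up to 70 and does not require employment. Even so, a usable unbiased comparison is within reach once controls are measured.

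**The case against.** **The plan is optional and sits in the Discussion.** This stands. The word may can fairly be read as covering the questionnaires as well as the physicians who would use them, so it goes too far to say that work questionnaires are definitely planned for the fencing group only. But this is the article's only description of collecting work outcomes, and dropping it leaves nothing described in its place.

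**Return to work and employability are not the same as levels of Work Ability.** Partly right. The Introduction lists them separately, and the Work Ability instrument may simply be unnamed in a condensed article. The Discussion nevertheless moves from work ability and its index straight to these questionnaires, and no other route is given.

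**The Secondary objective does not clearly promise a between-arm comparison of Work Ability.** The verb compare governs the preceding list, and Work Ability shares its sentence with provider attitudes. This stands as a reading of that sentence. The Discussion's aim of showing actual benefit still needs a comparator.

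**Controls receive all the mentioned parameters.** They do, but no work measure is among them, and the quality-of-life row of Table 4 names only the EORTC instruments.

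**Sleep quality.** A reader might infer that sleep quality cannot be compared either, because Table 4 has no sleep instrument. The article does not support that. The Secondary objective promises "sleep quality (both measured via specific questionnaires", and nothing restricts sleep to one arm. Table 4 is also not exhaustive: the Design section plans PREDIMED, whose "questionnaire will be completed both at the beginning and at the end of the study", and Table 4 omits it too. What remains is an unnamed instrument.

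**Conclusion.** The point holds for work outcomes. As described, their collection is optional and limited to the fencing arm, with no control-arm measure anywhere in the article. An effect on work outcomes therefore cannot be compared between arms, and any fencing-arm change would include recovery under usual care. The bias is the whole usual-care change, which the documents do not quantify. All 75 controls, half of the 150 women, would have no work data.

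This rests on two assumptions: that the full protocol does not already give controls a work questionnaire, and that work outcomes change to some degree under usual care. It concerns a secondary outcome and should be corrected. It does not threaten the primary objective or the sample size. The sleep questionnaire is a minor inconsistency between the Secondary objective and Table 4, and nothing more should be inferred from it.

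**What to change.** 1. In the Discussion, have the work questionnaires go to participants in both arms.
2. Add a named work-ability instrument to Table 4. The Work Ability Index, which the Discussion mentions, is one example.
3. Administer it in both arms at baseline and at the three-monthly assessments they share, and analyse the between-arm difference. State how women not in work at baseline are handled.
4. While editing Table 4, add the sleep questionnaire that the Secondary objective refers to.

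The cost is one short self-completed questionnaire at visits both arms already attend, with slight extra respondent burden and no added visits. The change should be in place before participants pass their baseline visit, because control-arm baselines that are missed cannot be recovered.
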